#### Secondary outcomes

As shown in Table 5, the secondary outcomes of interest will include MCH service coverage and process indicators of the *i-MoMCARE* intervention, adapted from previous studies [18, 29, 35]. We will measure these indicators to further determine the degree of effectiveness of the intervention.

**Table 5 Tab5:** List of secondary outcomes of interest in the *i-MoMCARE* trial

**Outcomes indicators and description**
**Maternal outcomes**
*Antenatal care (ANC)*
1. The proportion of mothers completing the first ANC visit timely and those having at least four ANC visits
2. The proportion of mothers receiving recommended supplements, HIV and syphilis tests, and immunization during ANC visits
3. The proportion of mothers visited at home or called by VHSGs at least three times during the pregnancy
4. The proportion of mothers with complications during their last pregnancy and seeking care from health providers or VHSGs
*Delivery*
1. The proportion of mothers delivered by a skilled provider and in a health facility
2. The proportion of mothers staying at least 3 days at a health facility after delivery for post-delivery care
3. The proportion of mothers delivering at less than 37 weeks of pregnancy (pre-term delivery)
4. The proportion of mothers delivering low-birth-weight babies (< 2.5 kg)
5. The proportion of mothers experiencing complicated delivery
*Postnatal care (PNC)*
1. The proportion of mothers with a postnatal checkup during the first 7 days after delivery by skilled health providers
2. The proportion of mothers with at least three PNC visits by the 23rd month of delivery
3. The proportion of mothers receiving counseling about body and hand hygiene, nutrition for the mother, breastfeeding, and risk symptoms for the mother and newborn during PNC visits
4. The proportion of mothers with complications within the first month of the last delivery and seeking care from skilled health providers or VHSGs
*Neonatal (0–28 days) outcomes*
1. The proportion of neonates breastfed within the first hour of birth
2. The proportion of neonates examined with the risk symptoms
3. The proportion of neonates visited and satisfactorily examined by VHSGs during their home visits after delivery
4. The proportion of mothers receiving satisfactory counseling about neonatal care from skilled health providers after delivery
5. The proportion of neonates with complications within the first month of the last delivery and seeking care from skilled health providers or VHSGs
*Young infant (2–12 months) outcomes*
1. The proportion of mothers exclusively (≥ 6 months) breastfeeding their child
2. The proportion of young infants receiving recommended vitamin supplements
3. The proportion of young infants fully vaccinated with basic antigens^a^
4. The proportion of young infants with severe diarrhea and receiving oral rehydration therapy from health providers or VHSGs within the last 2 weeks
5. The proportion of young infants with acute respiratory infections/fever and receiving care from health providers or VHSGs within the last 2 weeks
6. The proportion of young infants receiving growth monitoring checkups and follow-ups
*Young child (13–24 months) outcomes*
1. The proportion of mothers continuously (beyond 6 months) breastfeeding their child
2. The proportion of mothers receiving birth-spacing advice from skilled health providers
3. The proportion of young children fully vaccinated according to the national schedule^b^
4. The proportion of stunted, wasted, and underweighted children (under 2 years) (will be captured by anthropometric measures)
*Process indicators*
1. The proportion of days VHSGs and HC staff logging in to *i-MoMCARE* mobile phone and web-based application, respectively (login rate)
2. The proportion of scheduled tasks completed by VHSGs and HC staff in *i-MoMCARE* mobile phone and web-based application, respectively (task completion rate)
3. Number of pregnancies and births registered using mobile phones against the total number of pregnancies and births
4. Number of complicated maternal, newborn, and child cases identified against expected
5. Stock-out rate (proportion of times when a drug or equipment is unavailable when required, e.g., non-availability of antibiotics in case of child pneumonia)

*ANC* Antenatal care, *HC* Health center, *PNC* Postnatal care, *VHSG* Village health support groups

^a^A young infant aged 2–12 months is considered fully vaccinated if the infant has received the BCG vaccine, three doses of polio and DTP vaccines, and a single dose of measles vaccine [4]

^b^A young child aged 12–24 months is considered fully vaccinated according to the national schedule if the child has received all basic antigens and a birth dose of hepatitis B vaccine, a dose of IPV, three doses of hepatitis B and Hemophilus influenza type B vaccine (given as part of DPT vaccine), and three doses of the pneumococcal vaccine [4]

### Data collection and management

Data collection, entry, quality assurance, monitoring, and security maintenance will be supervised and coordinated by UHS’s Public Health Department, the lead implementer of the *i-MoMCARE* program. The Saw Swee Hock School of Public Health of the National University of Singapore (NUS-SSHSPH) will provide technical support to Cambodia-based implementing partners.

#### Quantitative data

##### Mobile and web-based applications

The process indicators will be collected from the web interface of the *i-MoMCARE* program during the intervention. Data from the mobile application will be linked to the web interface and stored in encrypted cloud storage hosted by the UHS. Given the high sensitivity of personal health data, we will develop a data management strategy for the data collected by the mobile application and web interface to ensure the data security and privacy and confidentiality of the participants. Data will be backed up regularly into encrypted computers. Only research team members will have access to the data.

##### Household survey and anthropometry measures

We will conduct household surveys at baseline and endline to measure the primary and secondary outcomes of interest in control and intervention arms. We have developed a household survey questionnaire (Additional file 2) based on the tools used in the Cambodia Demographic Health Survey (CDHS) 2021 and the National Guidelines for Implementing the Service Package of Antenatal, Delivery, and Postnatal Care [4, 29]. We will pre-test the tools before the data collection. Mothers of children aged 6–24 months and pregnant women aged 18–49 years will be eligible to participate in the surveys. The survey will collect household demographic information, durable assets, access to ANC, delivery, and PNC services, health insurance coverage, social health protection, health expenditures, and child anthropometric information. We will use an online platform to store the data and an electronic tablet installed with the data collection application equipped with Internet access to enter the data by trained interviewers. A village-level household population list from the population census in 2019 will be used as a sampling frame for household selection.

We will measure weight and height and check for edema of the eligible children (aged 6–24 months) to measure their nutritional status during the household survey. Weight will be measured in kilograms (kg) using the United Nations Children’s Fund (UNICEF) Uniscale with a precision of 100 g (one decimal point). Height will be measured using a length board from UNICEF in centimeters with a precision of one millimeter. The enumerators will measure height and weight twice. A research team member with a child nutrition background will train the interviewers to perform the anthropometric measurements. All enumerators will practice the anthropometric measurements during the pre-test. They will be instructed to calibrate the weighing scale before collecting data.

We will conduct data quality assurance exercises during and after data collection. The research team will review stored and regularly updated data on the server by synchronizing them with electronic tablets. Questions arising from the reviews will be directed to the data collection team leaders. After completing the data collection, the team will check the data set again for inconsistency, outliers, irrational magnitude, errors, and illogical skipped patterns in collaboration with the data collection team leaders. We will store the cleaned data in a desktop computer with a password at UHS’s Department of Public Health office.

#### Qualitative data

We will conduct KIIs, IDIs, and FGDs with the community and stakeholders recruited using the purposive sampling method at three study stages—gap analysis, pilot, and intervention. Tables 2, 3, and 4 show each stage’s estimated number of interviews. We will train the enumerators to conduct the interviews and write the discussion and field notes. We have developed the topic guides in consultation with the UHS and NMCHC. Interviews will be conducted face-to-face in Khmer and recorded using an audio recorder. The research team will transcribe the Khmer transcriptions and translate them into English for thematic analyses, save the recorded audio and transcriptions/translations on a password-protected computer, and keep the field discussion and notes in a locked cabinet in the study team’s office. We will assign unique identification numbers instead of participants’ identifiers to protect their privacy and confidentiality. Additional file 3 presents qualitative data collection tools.

### Analysis plan

#### Quantitative data

##### Data from household surveys, mobile applications, and web interface

We will use Stata 17 (StataCorp LLC, [name]) for quantitative data analyses. Since the randomization will be performed at the cluster level, all pregnant women and infants in the intervention arm will be eligible for the program. We will conduct intention-to-treat (ITT) analyses to examine the *i-MoMCARE*’s impact on outcomes of interest. Additional analyses will be per the study protocol analyses. We will analyze household data by considering cluster randomization design. The matched-pair method introduced in the earlier section is to achieve balanced randomization rather than representing a matched dataset when individual participants serve as their controls. Therefore, our analysis must consider this matching. We will test (i.e., Student’s *t*-test and chi-square test) the differences in the means or proportions of the maternal and child characteristics in the intervention and control arms at the beneficiary and cluster levels to observe balances in the study arms at baseline. In case of an imbalance in certain specific characteristics, we will apply a generalized estimating equation (GEE) approach to account for this imbalance. We will employ a difference-in-difference method using the GEE approach for all outcomes of mothers, pregnant women, and infants collected at baseline and endline. We will cluster standard errors at the village level to account for intra-cluster correlation in the characteristics of mothers. To account for multiplicity that may arise from testing multiple endpoints (i.e., primary and secondary outcomes) and lead to false rejection of the null hypothesis of no effect (type I error), we will apply the Bonferroni method and resampling-based method (i.e., bootstrapping) to obtain appropriate *p*-values [36].

To calculate children’s nutritional status, we will enter data on weight, height, sex, and date of birth into the Essential Nutrition Action software (ENA 2011) to compare the weight-for-age, height-for-age, and weight-for-height data to the international WHO reference standards. Data from the mobile phone application and web interface will be analyzed using a before-and-after method to determine the changes in the process indicators (Table 5).

We will conduct a sensitivity analysis to ascertain the effect size in our analyses. The GEE method has recently been criticized for inflating the type 1 error, resulting primarily from the incorrect standard errors obtained from the GEE method when the number of clusters is small [37]. Since the number of clusters in our study will be 10 ODs (< 30 clusters), we will conduct further analyses using the finite-sample corrected GEE bias correction [38, 39] and covariate adjustment methods [40, 41] to obtain the correct standard errors and make appropriate inferential analyses.

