### Randomization

The randomization will be done at the operational district level (cluster), the third tier of Cambodia’s health system. To address the issue of contamination that may arise and maintain comparability between the two arms (balanced randomization) at baseline, we performed a matched-pair selection of 10 provinces (five for each arm) out of the 25 provinces in Cambodia based on similar levels of MCH-SES index and NMCHC’s recommendations (Table 1). We used the principal component analysis approach [22] to construct the provinces’ MCH-SES index from a basket of indicators of ANC, delivery, and PNC from the Cambodia Demographic and Health Survey (CDHS) 2021 [4] and indicators of socioeconomic status from the National Population Census 2019 [23] and Cambodia Socioeconomic Survey 2019 (CSES) [24]. The indicators from CDHS 2021 included the proportion of pregnant women attending at least four ANC, the proportion of women delivering in a health facility, the proportion of women having a PNC visit in the first 2 days after delivery, the proportion of fully vaccinated (basic antigen) children aged 12–24 months, the proportion of fully vaccinated (according to the national schedule) among children aged 12–24 months, and proportion of children aged 12–24 months without vaccinations. The indicators from the population census 2019 included population density, literacy rate of the population aged 7 years and older, the proportion of the population aged 15 years and older with secondary education or higher, the proportion of households with electricity, and the proportion of households with piped water in a dwelling, while median monthly income per capita in thousand Khmer riels was from the CSES 2019.

**Table 1 Tab1:** List of matched-pair provinces with their respective MCH-SES indices

Pair	Matched province	MCH-SES index	Matched provinces	MCH-SES index
1	Kampong Speu	1.11	Kampong Chhnang	1.38
2	Pailin	0.37	Pursat	0.12
3	Kampot	− 0.17	Preah Sihanouk	0.15
4	Oddar Meanchey	− 1.07	Kampong Thom	− 1.34
5	Preah Vihear	− 2.75	Ratanak Kiri	− 7.77

*MCH* Maternal and child health, *SES* Socioeconomic survey

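### Baseline t and chi-square tests decide which characteristics are adjusted for: at beneficiary level they over-flag, and at cluster level they would miss the plainly unmatched pair 5

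*Protocol article*

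**What the plan says.** All references are to the protocol article.

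- **Balance tests.** The analysis plan for household survey data names Student's t-test and the chi-square test, applied to "the differences in the means or proportions of the maternal and child characteristics in the intervention and control arms at the beneficiary and cluster levels".
- **Consequence of the tests.** The next sentence reads: "In case of an imbalance in certain specific characteristics, we will apply a generalized estimating equation (GEE) approach to account for this imbalance". It names neither the characteristics nor what counts as an imbalance.
- **Main model.** Whatever the tests show, "We will employ a difference-in-difference method using the GEE approach for all outcomes of mothers, pregnant women, and infants collected at baseline and endline".
- **Matching.** The same paragraph says "Therefore, our analysis must consider this matching" and gives no method.
- **Sensitivity analyses.** Because there are only ten ODs, finite-sample corrected GEE is added, together with "covariate adjustment methods [40, 41] to obtain the correct standard errors and make appropriate inferential analyses". No covariates are named there either.
- **How pairs were formed.** Under Randomization, the investigators "performed a matched-pair selection of 10 provinces (five for each arm) out of the 25 provinces in Cambodia based on similar levels of MCH-SES index", together with recommendations from the national maternal and child health center. Table 1 lists the index for each pair; pair 5 is -2.75 and -7.77.

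**The concern.** Covariates should be chosen for what they are expected to predict, and before the data are seen. Here a baseline difference opens the door to adjustment, and significance tests are the named means of finding one. With ten randomized units, the set of adjusted characteristics, and hence the estimate, can turn on which tests happened to be significant.

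The two levels of testing also fail in opposite directions. Women in one OD resemble each other, so a test that treats them as independent over-flags. A comparison of five OD means with five others sees very little. The plan does not say which level governs if they disagree. Nor does a GEE in itself remove an imbalance; only the covariates put into it can do so.

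Meanwhile one imbalance is already printed in the protocol. Pairs were formed "based on similar levels of MCH-SES index", and pair 5 is far from similar.

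**Working it through.** **Inputs.** ICC 0.02, about 200 women per OD, five ODs per arm, 95% confidence, 85% power, 70% coverage, effect 13% (Sample size). Index values from Table 1.

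**1. Reproducing the protocol's sample size.** Read 13% as percentage points, so 0.70 against 0.83, with unpooled variance:

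- n = (1.960 + 1.036)² × (0.70×0.30 + 0.83×0.17) / 0.13² = 186.5 per arm.
- Design effect (DE) = 1 + (200 − 1) × 0.02 = 4.98.
- 186.5 × 4.98 = 928.9, i.e. 929, as stated. Then 1858 × 1.05 = 1950.9, i.e. 1951, as stated.

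So the protocol's own calculation carries a design effect of 4.98.

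**2. Beneficiary-level test that ignores clustering.** The true standard error is √DE times the one the test uses, so the false-flag rate is 2 × (1 − Φ(1.96/√DE)).

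| ICC | Women per OD | DE | False-flag rate |
|---|---|---|---|
| 0.02 (protocol) | 200 | 4.98 | 38.0% |
| 0.02 (protocol) | 185.8 (= 929/5) | 4.70 | 36.6% |
| 0.005 (assumed) | 185.8 | 1.92 | 15.8% |
| 0.05 (assumed) | 200 | 10.95 | 55.4% |

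For ten independent characteristics (an assumption), all at ICC 0.02 with 185.8 women per OD, the chance of at least one false flag is 1 − (1 − 0.366)¹⁰ = 99%. With a valid 5% test it would be 1 − 0.95¹⁰ = 40%.

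**3. Cluster-level t-test, five against five (8 df).** For a true imbalance of d between-OD standard deviations the noncentrality is d/√(2/5). Power is 29% at d = 1 and 55% at d = 1.5.

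**4. Table 1.** The absolute gaps in pairs 1 to 5 are 0.27, 0.25, 0.32, 0.27 and 5.02. Pair 5 is 5.02/0.32 = 15.7 times the next largest, and 5.02/6.13 = 82% of the total gap.

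- Pair 5 contributes 5.02/5 = 1.004 to the difference in arm means, with a sign fixed by its allocation.
- The other four contribute at most (0.27 + 0.25 + 0.32 + 0.27)/5 = 0.222 in either direction.
- Over all 2⁵ = 32 allocations the absolute arm difference therefore lies between 1.004 − 0.222 = 0.782 and 1.004 + 0.222 = 1.226.

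**5. Would the cluster-level test see it?** Take the most unbalanced allocation. The arm means are -0.384 and -1.610 and the variances 2.51 and 12.62, so SE = √((2.51 + 12.62)/5) = 1.74 and t = 1.226/1.74 = 0.70, giving p = 0.50. Across the 32 allocations p runs from 0.50 to 0.67. The extreme value inflates the variance that it is tested against.

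**6. Should the main model change too?** OD means were simulated (40,000 runs, 186 per OD, ICC 0.02, effect 0.13). The baseline–endline correlation of OD means, r, is not in the documents and is assumed. The table gives power for difference-in-difference against ANCOVA on the OD baseline.

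| r | Unpaired | Pairs kept (4 against 3 df) |
|---|---|---|
| 0 | 46% / 67% | 36% / 44% |
| 0.40 | 66% / 73% | 53% / 50% |
| 0.63 | 86% / 86% | 74% / 62% |
| 0.75 | 96% / 94% | 88% / 74% |

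Type I error was about 5% for every method.

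**The case against.** **The baseline is already used.** The difference-in-difference model applies to all outcomes without condition, so each outcome's baseline level enters whatever the tests show. The test rule governs additional covariates only. This stands, and it limits the reach of the point.

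**The covariate list belongs in the SAP, which is not shown.** The missing list alone would be no finding. The trigger, however, is stated in the protocol, and an SAP that followed it would inherit it.

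**The tests are only meant to observe balance, and no threshold is given.** True of the testing sentence. The sentence after it makes adjustment depend on an imbalance, and the tests are the only means named for finding one.

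**The 38% borrows the planning ICC of the coverage outcome for unnamed characteristics.** Fair, hence the range of 16% to 55%. Even its lower end is three times nominal.

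**Pair 5 may matter less than it looks.** The index is province-level, and one OD is drawn per province after urban ODs and those without Internet coverage are excluded. The national center's recommendations were a second matching criterion. Allocation within pairs is random, so a poor match costs precision and leaves the design valid. All of this stands.

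A reader might also infer that differencing is an error and should give way to ANCOVA. The documents do not support that. Differencing is valid under randomization, and which method has more power depends on an unknown correlation. With pairs kept, ANCOVA is ahead at r = 0 but behind from r = 0.40 upward. Nor can one say that nothing planned touches the imbalance: the matching is to be considered, and covariate adjustment is planned as a further analysis.

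**Conclusion.** The concern holds for the rule that lets baseline tests trigger adjustment. As named, the beneficiary-level tests flag chance differences about 38% of the time at the protocol's own ICC and cluster size. The cluster-level test would not flag pair 5 on the matching index under any allocation. The adjustment set would thus be data-driven and would still miss the one imbalance that the protocol displays.

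It does not extend to the main model, and the Table 1 gap suggests but does not prove imbalance between the ODs actually randomized.

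The figures assume equal OD sizes, a normal approximation for the beneficiary-level test, a two-sided 5% threshold (the protocol states none for these tests) and, for the 99% figure only, independent characteristics. The point is worth correcting because the change is nearly free, but it does not invalidate the design.

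**What to change.** 1. Report baseline balance descriptively at OD and beneficiary level, and remove the tests as the trigger for adjustment.
2. Before endline data are available, fix a short covariate list to be used whatever balance is observed, for example the MCH-SES index used for matching, or pair. Keep cluster-level terms few because there are ten clusters. Pair terms respect the matching but do not remove the gap inside pair 5. A linear index term addresses that gap but leans heavily on the single value of -7.77.
3. Keep difference-in-difference as the primary analysis if preferred. ANCOVA on the OD baseline is an option, to be chosen and justified in advance from an assumed correlation.
4. Add one pre-specified sensitivity analysis without pair 5. Say that it rests on four pairs (3 df, or 2 with one cluster-level covariate), so it shows direction and stability more than significance.

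**Cost.** Wording only, with no new data. Each cluster-level covariate uses one residual degree of freedom: from 8 to 7 unpaired, or from 4 to 3 with pairs kept.

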### Sample size

We used a sample size calculator for the cluster RCT and a practitioner’s guide to sample size and power calculation by McConnell and Vera-Hernandez [26] to estimate sample size and power for this study. Given the absence of similar studies in Cambodia, our assumptions were based on those used in a similar study in India with some adjustments. We assumed the intra-cluster correlation (ICC) to be 0.02 and the effect size of 13%, slightly below the 15% in India [18]. We observed that the MCH coverage index constructed from indicators of at least four ANC visits, PNC visits in the first 2 days after delivery, and complete immunization of children aged 12–24 months in 2021 in our selected provinces is at 70%, higher than the 36% of the MCH composite index in India [27]. Our cluster size was approximately 200, assuming there are two HCs per operational district, 10 villages per HC, and 10 mothers or pregnant women per village. The confidence level was set at 95%, while each arm consisted of five clusters. After obtaining a sample of 1858 mothers (929 per arm) and a power of 85%, we accounted for a 5% non-response rate and arrived at a sample size of 1951 mothers for both arms.

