#### Primary outcomes

VHSGs will facilitate the primary outcomes of interest throughout the continuum of care, including (1) the proportion of neonates/mothers visited at home by VHSGs at least twice within the first week of delivery, (2) the proportion of mothers receiving information from VHSGs regarding danger signs of newborn illnesses within the first week of delivery, and (3) the MNCH composite coverage index, consisting of four dimensions, namely maternal care, neonatal care, infant care, young childcare, and care-seeking when having complications.

The MCH composite index was initially introduced by Boerma et al. [31, 32]. It captures a complete continuum of care of mothers and children by including four dimensions: family planning, maternal and newborn care, immunization, and treatment of children. Following Modi et al. [27], we will exclude family planning to focus more on the role of the VHSGs in evaluating the effectiveness of mobile health technology. The three components will be equally weighted. The index will be calculated using the following formula: MCH-CI = 1/3 (¼ APNC + ½ IMMU + 1/3 TREAT), where APNC denotes antenatal and postnatal care, IMMU denotes immunization among children, and TREAT denotes the treatment of children. The index will vary between 0 and 100, with a higher index score indicating a higher MCH coverage. We will use the MCH coverage index to evaluate the effectiveness of the intervention. We have conjectured that the coverage rate should be well above 60% to be meaningful since earlier estimates of the compelling national coverage of maternal health services (ANC and facility delivery) and sick childcare (diarrhea, pneumonia, and fever) in 2014 were 56.4% and 59.1%, respectively [33]. Another recent study using a slightly deviated measure of the mother and infant care continuum shows that the national coverage was 49.4% [34].

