APNC will consist of four sub-components: (1) the proportion of mothers visited by VHSGs at least three times in the last pregnancy, (2) the proportion of mothers with at least four ANC visits in the last pregnancy and one tetanus vaccine injection, (3) the proportion of mothers delivered at a health facility (public or private), and (4) the proportion of mothers with at least three PNC visits in the last pregnancy. IMMU will consist of two sub-components: (1) the proportion of young infants aged 12–24 months fully vaccinated based on the national guideline with one dose of Bacillus Calmette–Guérin (BCG) vaccine for tuberculosis; three doses of polio vaccine given as oral polio vaccine (OPV), inactivated polio vaccine (IPV), or combination of OPV and IPV; three doses of diphtheria, pertussis, and tetanus (DPT) vaccine; and one dose of measles vaccine given as measles-rubella (MR) and (2) the proportion of young infants exclusively breastfed in the first 6 months. TREAT will consist of three sub-components: (1) the proportion of neonates with complications in the first month of the last delivery who seek care from VHSGs, (2) the proportion of infants aged two to 24 months with diarrhea in the last 2 weeks and receiving oral rehydration therapy (ORT) from VHSGs, and (3) the proportion of infants aged 2 to 24 months with acute respiratory infections in the last 2 weeks and seeking care from VHSGs.

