##### Analysis methods to handle protocol nonadherence and missing data 

We will adopt intention-to-treat analyses and imputation methods for missing data.

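### The primary MCH composite index is a group-level quantity, but the planned village-clustered GEE and the sample size do not treat it as one

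*Protocol article*

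**What the plan says.** Under Primary outcomes, the protocol article lists three primary outcomes: home visits in the first week, danger-sign information in the first week, and the composite coverage index. It then names the index as the measure for evaluating effectiveness. The formula is "MCH-CI = 1/3 (¼ APNC + ½ IMMU + 1/3 TREAT"), and the three components are to be equally weighted.

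The same section gives APNC four sub-components, IMMU two and TREAT three. All nine are proportions. The TREAT items are conditional on illness, for example "the proportion of infants aged two to 24 months with diarrhea in the last 2 weeks and receiving oral rehydration therapy (ORT) from VHSGs". No score for an individual woman is defined.

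Under Analysis plan, Quantitative data, the article states: "We will employ a difference-in-difference method using the GEE approach for all outcomes of mothers, pregnant women, and infants". It continues: "We will cluster standard errors at the village level", with the stated aim of handling correlation in mothers' characteristics. It also says that the analysis has to take the pair matching into account. The next paragraph adds small-sample GEE corrections because there are only 10 operational districts (ODs).

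On missing data the article says only: "We will adopt intention-to-treat analyses and imputation methods for missing data".

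The Sample size section works per mother: "We assumed the intra-cluster correlation (ICC) to be 0.02 and the effect size of 13" per cent, then "After obtaining a sample of 1858 mothers (929 per arm) and a power of 85" per cent. Its 70% baseline comes from an index of three indicators (antenatal visits, early postnatal visits, immunization), none of them conditional on illness.

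**The concern.** A regression with village-clustered errors needs a value of the outcome for each woman, or at least for each village. The index has no such value for nearly all women and, depending on how common the illnesses are, for many villages. An analyst applying the stated model to the index would have to improvise on a primary outcome after seeing the data.

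The obvious improvisations estimate different things. Averaging the items a woman happens to have changes the weights. Restricting to women or villages with all items discards most of the data. Treating an item that does not apply as missing, and imputing it, would assign care to children who were not ill. TREAT carries one third of the index, so the choice could matter to the main result.

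**Working it through.** **1. What the sample size treats as the outcome.** Inputs from the Sample size section: 70% baseline, 13% effect, ICC 0.02, cluster size 200, power 85%, 95% confidence (taken as two-sided). Reading 13% as percentage points gives 70% against 83%:

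- n per arm = (1.960 + 1.036)² × (0.70×0.30 + 0.83×0.17) / 0.13² = 186.53
- design effect = 1 + (200 − 1) × 0.02 = 4.98
- 186.53 × 4.98 = 928.9, so 929 per arm and 1,858 in total, as stated.

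The published figure is therefore that of a binary outcome observed once per mother.

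**2. Structure of the index.** From the formula, each item's weight is:

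| Component | Items | Denominator | Weight per item |
|---|---|---|---|
| APNC | 4 | mothers, last pregnancy | 1/3 × 1/4 = 1/12 |
| IMMU, vaccination | 1 | children aged 12–24 months | 1/3 × 1/2 = 1/6 |
| IMMU, breastfeeding | 1 | infants, first 6 months | 1/6 |
| TREAT, neonatal | 1 | neonates with complications | 1/3 × 1/3 = 1/9 |
| TREAT, diarrhea | 1 | 2–24 months, diarrhea in last 2 weeks | 1/9 |
| TREAT, respiratory | 1 | 2–24 months, acute respiratory infection in last 2 weeks | 1/9 |

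That is six denominators. It is in effect five if breastfeeding is scored retrospectively, because surveyed children are aged 6–24 months and have all passed six months.

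**3. How often the TREAT items exist.** The documents give no prevalence for the three conditions. I assume a common prevalence p of 5% to 20%, independence between conditions, and an eligible child for every woman. The last assumption favors the plan, since pregnant women are also surveyed. The Sample size section gives 10 women per village and 1,951 women per survey.

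- A woman has all three TREAT items with probability p³.
- A woman has none with probability (1 − p)³.
- A village has no case of one condition with probability q = (1 − p)¹⁰.
- A village lacks at least one TREAT denominator with probability 1 − (1 − q)³.

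| p | Women with all three (of 1,951) | Women with none | q | Villages lacking a denominator | Cases per item in an OD of 200 |
|---|---|---|---|---|---|
| 5% | 0.2 | 86% | 0.599 | 94% | 10 |
| 10% | 2.0 | 73% | 0.349 | 72% | 20 |
| 15% | 6.6 | 61% | 0.197 | 48% | 30 |
| 20% | 15.6 | 51% | 0.107 | 29% | 40 |

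**4. What averaging available items does.** A mother of a healthy child aged 12–24 months has APNC weight 4 × 1/12 = 1/3, IMMU weight 2 × 1/6 = 1/3 and TREAT weight 0. Rescaled to 1, APNC and IMMU each count one half. If the child is aged 6–11 months, only breastfeeding remains in IMMU, and the split is 2/3 APNC to 1/3 IMMU. Neither is the stated equal thirds.

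**5. Wider and unequal prevalences.** With 1,951/200 = 9.76 women per village, the share of village-rounds in which all three TREAT denominators exist runs from 0.3% (diarrhea 2%, respiratory infection 1%, neonatal complications 2%) to 83% (30%, 20%, 30%). With 195.1 women per OD, the corresponding OD-round probability is 0.83 at the lowest setting, 0.98 at 5/2/5% and at least 0.999 from 5/5/5% upward.

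**6. Whether a GEE can be fitted at all.** I simulated one trial with 10 ODs, 20 villages each and 10 women per village per round, two TREAT conditions at 10% and one at 5%. A full index existed for 2 of 4,000 women, 64 of 400 village-rounds and all 20 OD-rounds. A GEE difference-in-difference on the 20 OD values ran (10.6 points). So did a GEE on the nine stacked items with the index as a weighted contrast (10.8 points).

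**The case against.** A reader might infer that the planned GEE cannot be run on the index at all. The documents do not support that. The article never says that the index enters as a score per woman, it recognizes the 10 ODs as the clusters, and step 6 shows two GEE routes that work. The stacked version keeps the stated weights and, in that illustration, even the village clustering.

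A reader might also infer that the plan will impute care for children who were not ill. It does not say so. Such a child falls outside the item's denominator by definition and is not missing data. The general imputation sentence leaves this as a risk, not as a stated plan.

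Nor does the problem reach every primary outcome. The two first-week outcomes are ordinary binary measures and suit the planned model. The four APNC items share one denominator, and a few women could have all nine items. The village figures depend on prevalences that the documents do not give.

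Finally, the level at which a composite is computed is often left to the analysis plan, which is not shown. All of this limits the point but does not remove it. The article fixes one model and one clustering level for all outcomes and sizes the trial per mother, and neither fits an index defined only for groups.

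**Conclusion.** The stated analysis and the definition of the index do not match, and the article does not say at which level the index is computed. Used per woman or per village, the stated model does not estimate the equally weighted index. At an assumed 5% to 20% prevalence per condition, about 0 to 16 of 1,951 women have all three TREAT items, and 94% to 29% of villages lack at least one TREAT denominator. The wider assumptions move the village figure from over 99% down to 17%. The mismatch itself rests on the definitions alone. Its size rests on the assumed prevalences, on independence, and on every woman having an eligible child.

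It does not follow that the sample size is miscalculated on its own terms, since 929 per arm reproduces, or that any particular corrected sample size is needed.

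**What to change.** State in the protocol or analysis plan that the index is computed once per OD and survey round (20 values) from pooled numerators and denominators, using the stated weights. Take the endline-minus-baseline change in each OD, form the intervention-minus-control difference within each of the five matched pairs, and refer the mean difference to a t distribution with 4 degrees of freedom. An unpaired comparison of the 10 changes would have 8, but it would ignore the matching that the article says must be considered.

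Alternatively, fit a GEE to the nine stacked items, report the index as the stated weighted contrast of the item-level difference-in-differences, and use small-sample-corrected errors at OD level. Name one of the two in advance.

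Keep the person-level GEE for single binary outcomes. State that children without the illness are outside the TREAT denominators and are not imputed. Add a rule for an empty OD denominator: at the lowest prevalences in step 5, the probability that all 20 OD values exist is only 0.02, against 0.997 at 5% for each condition. Say in the Sample size section that the calculation is for a binary outcome per mother and stands in for the index.

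The cost is wording and slightly simpler code, with no new data. The drawback is few degrees of freedom, which is what 10 paired ODs provide.
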